### Recruitment

A non-probabilistic sampling procedure will be applied, where outpatients or hospitalized patients of the Public Mental Health Services who have presented some type of self-injurious behavior (with or without suicidal intent) the month prior to the evaluation will be invited to participate.

Therefore, the study will use a primary data source. For this, one of the psychiatrists of the research group will explain the purpose of the study and will invite each of the participants and their legal guardians to participate in the study. It will be made clear that regardless of the arm of the study to which each subject is assigned, at the end of the study all participants will be able to access the application free of charge. After the invitation, those who agree to participate will be interviewed by one of the members of the research group.

### Randomization

To perform the simple randomization of the treatments, the RStudio software version 1.4.1106 was used. For each of the hospitals, a patient ID vector was created (45 rows). Then, the ID of each hospital was randomly assigned a treatment, generated from a Bernoulli distribution with *p* = 0.5. Previously, a starting seed was set to ensure the reproducibility of the algorithm. The lists obtained were exported to a spreadsheet in Microsoft Excel. Each responsible investigator in each hospital received the list of the randomization sequence by email from the study coordinator ([name]).

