**Methods:**

To test the effectiveness, safety and level of engagement of the CALMA app in people aged 10 to 19 who are treated in mental health services of two public hospitals, we will conduct a parallel-group, two-arm randomized controlled trial. Participants will be assessed face-to-face and *via* video call at four timepoints: day-0 (baseline), day-30, day-60, and day-90. A total of 29 participants per group will be included. Change in the frequency of suicidal and non-suicidal self-injurious behaviors will be compared between groups, as well as the level of emotional dysregulation, level of app engagement and time of psychiatric admission during the follow-up period.

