### Participant timeline

Clinicians will be asked to draw up a list of patients who have presented self-injurious behavior in the last month. With this list, the patients will be identified on the days that they attend the control by their psychiatrist or psychologist of each Service. After the usual control of the patient, one of the members of the research group will explain the purpose of the study to the participant and legal guardian. Next, the researcher will give them a copy of the consent and/or assent to read carefully and invite them to participate in the study. After the invitation, those who agree to participate will be scheduled for a 30-min interview with one of the research group members.

The first interview will be face-to-face and it will determine if the participant meets the inclusion criteria and sign the informed consent. Then, a series of clinical and demographic data will be requested and the Spanish version of the Self-Injurious Thoughts and Behaviors Interview (SITBI) and the Difficulties in Emotion Regulation Scale (DERS) will be administered. At the end of the interview, the follow up interviews will be scheduled and those patients randomized to the intervention group will have the application downloaded to their cell phones. In addition, they will be given a brief 5 to 10-min tutorial on how the app works, they will be given written material on its functioning, and they will be directed to the website where there will be explanatory material.^1^

Follow-up interviews (day-30 and day-60): those will be conducted *via* video call according to the epidemiological context of the COVID-19 pandemic. During these calls, only the SITBI will be administered and participants will be asked if they have had any hospitalization due to suicidal behavior in that period, and if so, the date of admission. In the intervention group, to guarantee engagement with the CALMA app, the rater will explore whether or not the participant has used the application. In case of not using it, the obstacles and the alternatives to overcome them will be determined through a brief protocol (DBT missing links strategy) to reinforce the use of the application during the next evaluation period. At the same time, the technical team will work throughout the study to guarantee the proper functioning of the app.

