### Sample size

The sample size was calculated using the G*Power 3.1.9.4 statistical software according to the main objective. Considering a confidence level of 95%, a power of 80% and an effect size *d* = 0.85, 25 individuals per group are needed to detect a significant difference in the median frequency of self-injurious behaviors with the two tailed Mann–Whitney U test. Assuming a proportion of lost in the follow-up of 15%, then the study would have to start with 29 individuals per group.

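### The randomisation sequence was emailed to the responsible investigator at each recruiting hospital, with no separation from recruitment described, so upcoming assignments can be known before invitation, eligibility, consent and baseline

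*Protocol article*

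**What the plan says.** All references are to the protocol article.

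- **Randomization.** Simple randomisation was done in RStudio. For each hospital a vector of 45 patient IDs was created, and each ID was "randomly assigned a treatment, generated from a Bernoulli distribution" with p = 0.5. The lists went into an Excel sheet, and "Each responsible investigator in each hospital received the list of the randomization sequence by email from the study coordinator". The section is written in the past tense.
- **Recruitment.** Sampling is non-probabilistic. A psychiatrist of the research group invites patients and guardians. This section is in the future tense.
- **Participant timeline.** Treating clinicians draw up a list of candidates, and a research-group member explains the study. "The first interview will be face-to-face and it will determine if the participant meets the inclusion criteria". Consent is signed at that visit, then clinical data, SITBI and DERS are collected, and at the end of the visit the app is installed for those randomised to it.
- **Abstract (Methods).** "A total of 29 participants per group will be included". The Sample size section derives this from "an effect size *d* = 0.85" and a statement that "25 individuals per group are needed to detect a significant difference", then allows for 15% loss.

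**The concern.** Randomisation protects the comparison only if nobody who influences entry can know the next assignment. A readable ID-to-treatment table at the recruiting hospital removes that protection for anyone who can see it. Several features of this trial make foreknowledge matter:

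- Whom to invite, and when, is discretionary.
- Eligibility has elements of judgement, such as planning to continue treatment for three months.
- Baseline SITBI frequency is obtained by interview and enters directly into the outcome, because the Statistical analysis section compares change from baseline.
- The comparison is app versus no app, and follow-up raters ask intervention participants about app use, so the arm is visible after entry.
- The research group developed the app.

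If patients were steered by arm, or baseline counts were coloured by knowledge of the arm, the groups would differ from the start in ways the planned unadjusted t or Mann–Whitney comparisons cannot remove. Adjustment would not reliably repair selection on unmeasured severity either.

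A lesser matter is that independent coin flips do not deliver the planned equal arms.

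**Working it through.** **Concealment: the order of events.** No arithmetic applies, so the sections are set side by side.

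1. The sequence is generated and the list emailed to each hospital's responsible investigator (Randomization).
2. Clinicians list candidates and a research-group member approaches them (Participant timeline, Recruitment).
3. At the first interview eligibility is settled, consent signed, and SITBI and DERS administered (Participant timeline).
4. The app is installed at the end of that interview.

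On the article's own tenses, step 1 precedes the rest. Step 4 shows that the arm is acted on after baseline, but it does not hide an assignment that was already readable at the site. The article does not say how IDs are matched to patients. If they are issued in order, the next arm can be read off; if not, a list holder could choose the ID. No envelope, central release or independent holder is mentioned.

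**Arm sizes: the plan's own figure first.** Inputs from Sample size: two-sided alpha 0.05, power 80%, d = 0.85, Mann–Whitney. Using noncentral-t power with n multiplied by the asymptotic relative efficiency (ARE) of the Mann–Whitney test, the requirement per group is 23 (t-test), 24 (normal parent, ARE 3/π) or 27 (minimum ARE 0.864). The stated 25 lies within two patients of each. For loss, 25 × 1.15 = 28.75, which rounds up to the stated 29; 25 / 0.85 = 29.4 would round up to 30.

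**Chance of the planned split.** With 58 randomised, one arm is Binomial(58, 0.5):

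- P(29/29) = C(58,29) / 2^58 = 0.104
- P(25/33 or more unequal) = 0.358
- P(24/34 or more unequal) = 0.237
- 95% range of one arm: 22 to 36

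**What imbalance costs.** With m₁ = 0.85·n₁·ARE, m₂ = 0.85·n₂·ARE, df = m₁ + m₂ − 2 and noncentrality 0.85·√(m₁m₂/(m₁+m₂)), where the first 0.85 is retention and the second is d:

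| Split | Power, ARE 3/π |
|---|---|
| 29/29 | 81.4% |
| 25/33 | 80.7% |
| 23/35 | 79.7% |
| 21/37 | 78.3% |
| Averaged over Binomial(58, 0.5) | 80.7% |

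The average cost is 81.4 − 80.7 = 0.7 points. With ARE 0.864 it is 77.3 − 76.5 = 0.8 points before finer rounding (0.7727 − 0.7654 = 0.0073).

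**If enrolment ran until both arms reached 29** (a rule the article does not state), the expected total would be about 64. The chance that both arms have reached 29 is 0.88 by 70 patients and above 0.99 by 90, the combined length of the two lists.

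**The case against.** The strongest defence is that nothing in the article says the list holder invites, screens or interviews anyone. Invitation is by a research-group psychiatrist, interviewing by a research-group member, and the Safety procedure names the interviewer, the study coordinator and the collaborator at each centre as separate roles. It is also unclear whether a hospital received both lists or only its own 45 rows. This stands as far as it goes. A reader might infer that recruiters did know each next assignment, or that allocation was in fact subverted; the document supports neither. It supports only that assignments can be known at the site, with no safeguard described. One hospital's own list is enough for that.

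Second, the written order already puts installation after baseline. That weakens the worry about baseline recording, but only if the interviewer has not seen the list, and the article does not say so.

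Third, one might call this a detail an article leaves to the full protocol. But the article states its release mechanism, and that stated mechanism is the problem.

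Fourth, simple randomisation is valid, unbiased and unpredictable, which is useful in an open trial. A reader might take the Bernoulli scheme as contradicting 29 per group or as seriously weakening the trial. It does neither: 29 is the number to start with, the 90 rows leave room to exceed 58, and the power cost is small. What remains is a gap, since no total or stopping rule links the scheme to the planned arm sizes.

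**Conclusion.** The concealment point holds and must be fixed before further enrolment: a pre-generated list was sent to the recruiting sites, and no separation from recruitment or staged release is described. This is an exposure to selection bias and to biased baseline recording, not evidence that either occurred, and its size cannot be derived from the document. The conclusion assumes only that the emailed list was readable on receipt; the article mentions no masking.

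The arm-size point is minor. An exact 29/29 split has probability about 0.10 if 58 are randomised, and the average power cost is about 0.7 points under the stated d, 15% loss and a normal-parent Mann–Whitney approximation. Chance imbalance in numbers is not bias, and on its own it would not require a change of scheme.

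**What to change.** 1. Withdraw the site-held lists.
2. For participants not yet enrolled, generate a fresh sequence held by the study coordinator, provided that person takes no part in recruitment, or by someone else outside it. Release one assignment at a time, only after consent, eligibility, baseline SITBI and DERS are recorded.
3. Report who had access to the emailed list and from when. If anyone was enrolled under it, say how many; concealment cannot be restored for them.
4. Settle arm sizes at the same time: either state a total of 58 and accept unequal arms, or build the new sequence in randomly sized blocks stratified by hospital. Do not close one arm once it reaches 29, because every later assignment would then be certain.

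The cost is a short release step per participant and an amendment to be notified to the ethics committees. If enrolment has begun, the trial will contain two allocation schemes, which should be disclosed. Blocks are partly guessable in an open trial; random block sizes and release by someone outside recruitment limit this.

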### Data management

All research data collected in this trial will be stored using a unique participant ID code, and will be stored in numerical order and stored in a secure and accessible place and manner in the Institute of Pharmacology od the School of Medicine of the University of Buenos Aires. Participant files will be maintained in storage for a period of 3 years after completion of the study.

The data manager will be responsible for uploading the collected data to a secure database, and will be responsible for securely transferring data to the research team. Data will be exported into appropriate statistical software for analysis. Only authorized study team members are able to view data. If there a rationale (e.g., participant request, unexpected adverse events, aggregate data indicates self-harm above the rates expected from this group) the research team will make the decision to terminate the trial if necessary. All adverse events attributable to a study intervention will be recorded and reported to the ethics committee of each institution. Participants may be withdrawn from the study if they experience a serious adverse event that is attributable to a study intervention or procedure, or means they can no longer participate in the study. Participants may also self-withdraw consent to take part. Participants that are withdrawn from the study will not be replaced.

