#### Secondary specific objectives

Analyze the frequency of self-injurious thoughts in the participants who receive the application with the frequency in those who do not receive the app.Establish that there is no increase in the frequency of self-injurious thoughts and behaviors in those participants who receive the application compared to the baseline levels at study onset.To explore whether the effectiveness of CALMA in reducing the frequency of self-injurious thoughts and behaviors is mediated by improved emotional regulation.Describe the levels of app engagement by the adolescent participants who used it during this study.To compare the time to psychiatric admission during the follow-up period in the participants enrolled who received the app with those participants who did not receive the app.

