### Statistical analysis

To describe the sociodemographic characteristics of the patients in the two groups, absolute and relative frequencies (%) will be used for the qualitative variables, and the mean and standard deviation will be used for the only quantitative variable (age) if it presents a normal distribution according to the Shapiro–Wilk test. In case of presenting a non-normal distribution, the median and the interquartile range will be computed.

To compare the sociodemographic characteristics between the groups, the chi-square or Fisher’s exact test will be used for the qualitative variables, and the student’s t-test or the Mann–Whitney U test will be computed for the quantitative variable.

For all patients and at each follow-up moments, the difference between the frequency of each suicidal behavior and the baseline frequency will be calculated. Then it will be evaluated if these differences follow a normal distribution (Shapiro–Wilk test). In this case, the mean differences for each behavior between both groups will be compared using the t-Student test. Otherwise, the medians will be compared with the Mann–Whitney U test. The *p*-values obtained will be corrected according to the Bonferroni criterion.

To assess whether the change in emotional regulation mediates the change in the frequencies of each suicidal behavior, the difference between the value of the DERS scale at the last follow-up and the baseline will be calculated, and the Sobel test will be used on a regression model whose dependent variable will be the difference in the frequency of each behavior and the independent variable will be the treatment. Previously, the probability distribution of the quantitative variables will be evaluated and it will be considered whether it is necessary to carry out any transformation of data to guarantee compliance with the assumptions of the regression model.

Both for the frequencies of the different suicidal behaviors and for the DERS scale, the missing values will be imputed according with the multiple imputation method using chained equations (MICE) with appropriate models for each variable to be imputed, considering sociodemographic characteristics, the hospital of recruitment and the baseline measurements of frequencies and DERS scale as independent variables.

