Regarding acceptability, the UEQ Data Analysis Tool offers a benchmark to classify the application in 5 categories of 6 scales: excellent, good, above average, below average and bad allowing conclusions to be drawn about the relative quality of CALMA compared to other products.^2^

To evaluate and compare the time to readmission in patients enrolled during hospitalization, a Cox regression model will be adjusted, considering the treatment of each patient as the independent variable. For this, the time elapsed from study entry to readmission (event) or to loss of follow-up or final of the study (censoring) will be calculated. In all cases, a value of *p* less than 0.05 will be considered significant. Statistical analysis will be performed with RStudio 1.4.1106.

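### The withdrawal provision lets participants leave the study, not only the app, after an attributable serious adverse event, so later outcomes of harmed CALMA users could be lost and imputed as typical

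*Protocol article*

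**What the plan says.** The protocol article's Data management section gives the provision at issue: "Participants may be withdrawn from the study if they experience a serious adverse event that is attributable to a study intervention or procedure". The same sentence adds a second ground, a serious adverse event that "or means they can no longer participate in the study". The section continues: "Participants that are withdrawn from the study will not be replaced". It also says: "All adverse events attributable to a study intervention will be recorded and reported to the ethics committee of each institution".

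Under Trial design, the control arm continues usual care and does not receive the app.

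Under Statistical analysis, for the behaviour frequencies and the DERS, "the missing values will be imputed according with the multiple imputation method using chained equations (MICE"), with the predictors described as "considering sociodemographic characteristics, the hospital of recruitment and the baseline measurements of frequencies and DERS scale as independent variables". Randomised arm, adverse-event status and earlier follow-up values are not in that list. The Cox model for readmission measures time to the event or "to loss of follow-up or final of the study (censoring").

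One secondary objective is to "Establish that there is no increase in the frequency of self-injurious thoughts and behaviors in those participants who receive the application", judged against their own baseline.

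**The concern.** The provision acts on study participation, not on use of the app. Because a separate ground covers people who cannot continue, the attributable-event ground reaches people who could still be interviewed.

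An event attributable to the intervention can occur only where the intervention is given, which is the CALMA arm. Participants enter because of self-injurious behaviour in the preceding month, so a serious event in this trial may itself be an attempt, self-injury or an admission. Those are the trial's own outcomes. Withdrawal on this ground would therefore depend on outcome and fall on one arm.

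Two analyses are exposed: the between-arm comparison of change in frequency at each follow-up, and the objective of showing no increase from baseline among app recipients. The second is the more sensitive, because its purpose is to detect deterioration in app users.

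**Working it through.** **Inputs from the protocol article (Sample size):** 29 per group at the start, 25 evaluable, 15% loss, d = 0.85, two-tailed Mann–Whitney, 5% level, 80% power.

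**Reproducing the plan's figure.** Noncentral-t power with the Mann–Whitney efficiency for normal data (3/π) needs 24 per arm, with 82.0% power at 25. With the minimum efficiency (0.864) it needs 27, with 77.9% power at 25. The stated 25 lies between. For dropout, 25 × 1.15 = 28.75, which rounds up to 29; 25 / 0.85 = 29.4 would give 30. The stated 29 is close enough to serve as the denominator below.

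**Assumptions, not in the document:** k = 1 to 4 app users are harmed; each has an excess of h = 1 to 3 SD in follow-up frequency; all of them are withdrawn before the visit analysed; the app has no other effect; scores are normal with SD 1 and a baseline to follow-up correlation of 0.5. The change score then also has SD √(1 + 1 − 2 × 0.5) = 1.

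**Harm visible with full follow-up.** The app-arm mean change moves by k × h / 29. The smallest case is 1 × 1 / 29 = 0.034 and the largest is 4 × 3 / 29 = 0.414.

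**Harm visible after withdrawal and imputation.** This was simulated with multiple imputation from baseline (5 imputations), using 3,000 runs for full follow-up and 1,500 for withdrawal. The columns show the between-arm difference in mean change, where positive means worse on CALMA.

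| k | h | k × h / 29 | Full follow-up | Withdrawn and imputed |
|---|---|---|---|---|
| 1 | 1 | 0.034 | 0.036 | −0.004 |
| 1 | 3 | 0.103 | 0.111 | −0.002 |
| 2 | 2 | 0.138 | 0.142 | 0.013 |
| 3 | 3 | 0.310 | 0.307 | −0.011 |
| 4 | 1 | 0.138 | 0.143 | 0.006 |
| 4 | 3 | 0.414 | 0.414 | 0.004 |

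The Monte Carlo standard error in the last column is about √(2/29) / √1500 = 0.263 / 38.7 = 0.007, so its entries are indistinguishable from zero. The app arm's own change from baseline behaves the same way: for k = 4 and h = 3 it falls from 0.413 to 0.004.

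**Why imputation does not repair this.** The listed predictors are fixed at entry, so a harmed user is imputed as a typical participant with the same baseline. Adding arm alone would not help, because the app users still observed are the unharmed ones.

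**Scale.** Relative to d = 0.85, the masked harm is 0.034 / 0.85 = 4% to 0.414 / 0.85 = 49% of the design effect. For one user it is at most 0.111 / 0.85 = 13%.

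**The case against.** Several points on the other side stand and limit the conclusion.

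- **Withdrawal is discretionary.** A reader might infer that the worst app-arm outcomes are removed automatically. The text says only that participants may be withdrawn, and nothing says that data collected earlier are discarded. An event disclosed at an interview is in that visit's SITBI; the loss concerns later values.
- **Harm is not hidden altogether.** Attributable events are recorded and go to the ethics committees, and the research team may terminate the trial if aggregate self-harm exceeds the expected rate. Participants also remain under the Mental Health team. What can be masked is harm in the SITBI and DERS analyses.
- **Controls can be withdrawn too.** Study procedures such as interviews apply to both arms, and so does the second ground. Only the intervention-attributable ground is one-sided.
- **The admission analysis is less exposed.** An admission is itself the Cox event, so one that occurs before withdrawal counts. Only a later admission after a different kind of event would be censored, and the model as described covers those enrolled during hospitalization.
- **Non-replacement is not a defect.** It preserves the randomised groups.
- **No event rate is given,** and the Ethics section calls the app's additional risk low. The values of k and h are assumptions.

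A reader might also want to quote an inflated false-positive rate. Removing exactly the worst 1 to 4 app users, with a complete-case t-test at an uncorrected 5% level, gives false findings in favour of the app in 4.6% to 18% of trials instead of 2.5%. That is not the planned analysis, which uses multiple imputation, Mann–Whitney where data are non-normal, and Bonferroni correction. With Bonferroni over an assumed 15 tests (5 behaviours × 3 visits), the per-test rates are 0.5% to 2.7%, against a nominal 0.05 / 15 / 2 = 0.17%. The direction of the bias survives; the headline rate does not.

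Finally, a journal article may leave post-withdrawal data collection to the full protocol. Silence alone would be no finding. Here, however, the article states a provision, and as worded it ends study participation.

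**Conclusion.** The point holds in a limited form. The article permits withdrawal from the study on a ground whose intervention-attributable part can arise only under CALMA and may be tied to outcome. The stated imputation predictors could not recover what is lost. When the provision is used in this way, the bias favours CALMA in both the between-arm comparison and the no-increase objective.

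The size is conditional. Under the assumptions of 1 to 4 harmed and withdrawn users of 29 and an excess of 1 to 3 SD, about 0.03 to 0.41 SD of true harm disappears, or 0.03 to 0.11 SD for a single user. The calculation uses normal scores and mean differences. Real frequencies may be skewed, and with a rank test the effect would depend more on how many users are withdrawn than on how badly they fared.

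The documents do not support the conclusion that harm would go unrecorded or that removal is mandatory. Should fix, moderate severity.

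**What to change.** In Data management, state that if use of the app is stopped after an adverse event, this does not end follow-up. The participant keeps the scheduled day-30, day-60 and day-90 SITBI, the day-90 DERS and the admission questions, and is analysed in the randomised arm, unless consent is withdrawn or interview is impossible. Add that withdrawals and their reasons will be reported by arm.

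This concerns data collection only. It proposes nothing about when use of the app should stop.

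The cost is a sentence or two of text. The interviews are already scheduled. The downside is that a few participants continue short interviews after they have stopped the app.
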